## Abstract

**Abstract:**

Lynch syndrome (LS) is the most common cause of inherited colorectal cancer (CRC) and confers a high lifetime risk of CRC estimated to be up to 60%. Colonoscopy is recommended every 2 years in LS patients above the 20–25-year-old age bracket, and every year when colonic neoplasia has been detected. Efficient chemoprevention has the potential to represent a cost-effective intervention in these high-risk patients and could allow a delay in colonoscopy surveillance. Several epidemiological studies have shown that regular use of low dose aspirin is associated with a 20 to 30% reduction in the risk of sporadic colonic adenomas and colorectal cancer regardless of family risk. However, in recent large randomized trials in specific populations, aspirin use showed no protection for colorectal cancer. A prospective randomized CAPP-2 trial evaluated the effect of aspirin use in LS patients. The primary analysis of this trial showed no significant decrease in CRC in LS patients under daily aspirin. However, a preplanned secondary analysis after an extended follow-up showed a significant reduced risk of CRC in the aspirin group in the per-protocol analysis. The real effect and clinical benefit of aspirin are still to be consolidated in this population. The AAS-Lynch trial—a prospective, multicentric, double-blind, placebo-controlled, randomized clinical trial—was designed to investigate if daily aspirin therapy, at a dose of 100 or 300 mg, would decrease the occurrence or recurrence of colorectal adenomas in patients under 75 years of age, compared with placebo.

**Trial registration:**

ClinicalTrials.gov NCT02813824. Registered on 27 June 2016. The trial was prospectively registered.

## Introduction

Lynch syndrome is the most common cause of inherited colorectal cancer. It is linked to germline alterations in mismatch repair genes that confer a high lifetime risk of colorectal cancer estimated to be as high as 60%. Most colorectal cancers arise from asymptomatic adenomas. Early detection and removal of adenomas can prevent their transformation into cancers. Colonoscopy is recommended every 2 years in Lynch syndrome patients above the 20–25-year-old age bracket, and every year when colonic neoplasia has been detected [1]. Efficient chemoprevention has the potential to represent a cost-effective intervention in these high-risk patients and could allow a delay in colonoscopy surveillance. Aspirin therapy decreases the risk of colorectal cancer in experimental models. Multiple mechanisms have been reported to explain this effect [2]. Several epidemiological studies have shown that the regular use of low dose aspirin (75 to 300 mg/d) is associated with a 20 to 30% reduction in the risk of sporadic colonic adenomas and colorectal cancer regardless of family risk [3]. Seven randomized controlled trials (RCT) evaluating adenoma recurrence are available [4–10]. Five out of seven trials showed a significant decrease in neoplasia recurrence [4–6, 8, 10]. A meta-analysis of four of these studies confirmed a decrease in colorectal adenoma recurrence [11]. In a pooled analysis of cardio-vascular prevention RCTs, and in a meta-analysis, daily aspirin was associated with a reduced risk of CRC and CRC associated mortality [12]. However, in two large, recent, randomized trials in diabetic patients and in healthy elderly patients, aspirin use showed no protection for colorectal cancer [13, 14]. The Colorectal Adenoma/carcinoma Prevention Programme 2 (CAPP-2) evaluated aspirin 600-mg (300 mg b.i.d) effect in LS patients. The primary analysis of this prospective randomized trial showed no significant decrease in CCR risk in LS patients under daily aspirin [15]. However, a preplanned secondary analysis after an extended follow-up (mean 56 months) showed a significantly reduced risk of CRC in the aspirin group in the per-protocol analysis [16]. In this study, the endoscopic follow-up was sub-optimal with a relatively low detection rate of colorectal neoplasia compared to the actual reported rate [17], or the chromo-endoscopy derived rate [18]. The exact effects and clinical benefits of aspirin therapy are still to be consolidated in LS patients. Notably, aspirin’s preventive benefits are expected to outweigh its putative adverse effects in these high-risk patients.

We designed the AAS-Lynch trial, which is a prospective, multicentric, double-blind, placebo-controlled, randomized clinical trial, to investigate whether the daily use of aspirin, at a dose of 100 or 300 mg, in LS patients under 75 years of age, would decrease the occurrence or recurrence of colorectal adenomas, compared with placebo. This trial will also investigate the role of the gut microbiota in adenoma apparition or recurrence in LS patients.

## Methods

### Eligibility criteria

Eligible subjects are adults aged 18 to 75 years with LS carrying a defined “mismatch repair” gene mutation or, when no characteristic alteration had been found, with a personal or family history of LS according to modified Amsterdam criteria (CRC diagnosed before 50 years of age; presence of synchronous or metachronous colorectal or other LS-related tumors regardless of age; CRC with MSI-high histology diagnosed in a patient who is younger than 60 years of age; CRC diagnosed in a patient with one or more first-degree relatives with a LS-related cancer which was diagnosed under 50 years of age; and CRC diagnosed in a patient with two or more first- or second-degree relatives with LS-related cancer regardless of age). Detailed inclusion and exclusion criteria are presented in Table 1.

**Table 1 Tab1:** AAS-Lynch eligibility criteria

Inclusion criteria	Exclusion criteria
- Men and women with Lynch syndrome with an alteration of “mismatch repair” genes or when no characteristic alteration has been found, with a personal or family history of Lynch syndrome according to modified Amsterdam criteria. - Aged over 25 or 18 years of age in cases with an early family history, with an indication for colonoscopic surveillance every 2 years - Under 75 years old. - Performing a colonoscopy within 180 days before inclusion, with removal of all endoscopically resectable polyps. - No regularly use of aspirin throughout the (7 consecutive days for at least 3 weeks per year or more than 21 days throughout the year). - Effective contraception for women of, defined by a hormonal method or IUD or surgical sterilization of the patient or her partner - Patient affiliated to a social security (excluding AME) or entitled - Patient who has given his consent to participate by signing the consent of the study	- Total colectomy - Adenomatous polyposis associated with known alteration of APC gene or MYH gene - Allergy to aspirin (including a history of asthma induced by the administration of salicylates or substances of similar activity, especially nonsteroidal anti-inflammatory drugs) - Allergy known to indigo carmine used for chromoendoscopy - Indication of prolonged treatment (prevention of atheromatous risk) or repeated treatment (recurrent migraine) with aspirin or other nonsteroidal anti-inflammatory drug (NSAID) - Abnormality of hemostasis or coagulation (including gastrointestinal hemorrhage, history of hemorrhagic stroke and thrombocytopenia) - Indication of long-term treatment with anticoagulant antiplatelet agents, anagrelide or uricosuric agents- History of digestive ulcer - Digestive hemorrhage related to ulcerative disease in the 12 months prior to inclusion - Gastric pathology deemed significant by the investigator and not corrected by appropriate treatment - Uncontrolled high blood pressure - Renal insufficiency (creatinine clearance < 30 ml/min) - Severe hepatic insufficiency (defined by a PT < 70%) - Severe uncontrolled heart failure - Known failure of G6PD deficit - Recent diagnosis of colorectal cancer requiring specific management - Presence of menorrhagia and not corrected by appropriate treatment - Pregnancy or breastfeeding - Any disease that may interfere with the follow-up provided by the protocol or invalidate the proper understanding of the protocol information and informed consent - Patient under the protection of justice - Participation in another therapeutic clinical trial in the 12 weeks prior to inclusion

### Intervention

A centralized randomization with stratification by age (< or ≥ 45 years) and center will be performed. It was not possible to obtain the 2 doses of aspirin (100 and 300 mg) with the same aspect; therefore, 2 different types of placebo tablets were used: one similar to the 100-mg aspirin tablet and the other similar to 300-mg tablet. Patients and investigators could identify the size of the tablet without knowing the assignment arm (aspirin or placebo). Patients are randomized to one of the four treatment conditions: aspirin 100 mg, aspirin 300 mg, placebo of aspirin 100 mg, and placebo of aspirin 300 mg, according to a ratio 1: 1: 1: 1 using a previously established randomization standardized protocol. A total blind would have required the daily intake of 2 different tablets (1 active and 1 placebo or 2 placebos). This choice was made to favor compliance by reducing the number of tablets prescribed. Patients and investigators can therefore identify the size of the tablet but without knowing the assignment arm (aspirin or placebo) (protocol version 3.0 dated 2 June 2017).

Circumstances under which unblinding is permissible are severe digestive hemorrhage, traffic accident, and another situation requiring knowing if the patient is on aspirin. The procedure for revealing a participant’s allocated intervention during the trial consists in calling the project manager or, in case of emergency, the poison control center at Fernand Widal Hospital.

### Primary end-point

The primary end-point is defined as the number of patients with at least one adenoma detected during planned surveillance colonoscopies with chromo-endoscopy at 24 and 48 months. Additional colonoscopies will be performed as required after initial colon clearance at inclusion with complete polyp removal.

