### Secondary end-points

The secondary end-points are defined as the adenomatous polyp burden (calculated as the sum of adenomatous polyps diameters as measured during planned surveillance colonoscopies); the delay between the inclusion and the first observed adenoma; the number of patients who presented with an adenoma during the follow-up according to the affected gene (MLH1, MSH2, MSH6, PMS2, other or no abnormality identified); the number of patients with sessile serrated adenoma, colon cancers diagnosed, and post-colonoscopy colon cancer (diagnosed between two planned surveillance colonoscopies); and time of apparition.

The quality of bowel cleansing, the number of chromo-colonoscopies performed in follow-up sessions, the number of remaining tablets in blisters, and side effects are reported.

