#### Follow-up visits

Six follow-up visits, interspersed at 6-month intervals, will be scheduled for the 4-year follow-up period: M6, M12, M18, M24, M30, and M36 (Table 2). During these visits, the patient will be provided with the next course of medication and compliance will be monitored. Medical examinations will be performed and additional colonoscopies scheduled as necessary. Urine pregnancy tests will be performed as described previously. Patients will be asked to report on any side-effects they had experienced as well as if they are undergoing other treatments, including self-medication. Further compliance and side-effect data will be collected, via telephone call, approximately 3 months before each follow-up visit.

**Table 2 Tab2:** Research timeline

	V0, inclusion	V1, M0	V2, M6	V3, M12	V4, M18	V5, M24	V6, M30	V7, M36	V8, M42	V9, M48
Protocol information	**X**									
Informed consent	**X**									
Antecedent	**X**									
Clinical exam	**X**		**X**	**X**	**X**	**X**	**X**	**X**	**X**	**X**
Blood analysis	**X**									
Chromo-colonoscopy	**X (< 6 months)**			**If necessary**		**X**	**If necessary**			**X**
Stool collection		**X**								**X**
Nutritional survey	**X**	**X**								
Physical activity survey	**X**	**X**								
Quality of life survey		**X**								**X**
Blood drops blotting paper		**X**								
Pregnancy test		**X**	**X**	**X**	**X**	**X**	**X**	**X**	**X**	**X**
Randomization		**X**								
Treatments dispensation		**X**	**X**	**X**						
Adverse effects			**X**	**X**	**X**	**X**	**X**	**X**	**X**	**X**
Compliance observation			**X**	**X**	**X**	**X**	**X**	**X**	**X**	**X**

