Recruitment status	Recruiting
Primary outcome(s)	Number of patients with at least one adenoma seen on chromo-endoscopy 48 months after complete withdrawal of polyps and initiation of treatment (aspirin or placebo) [time frame: 4 years]
Key secondary outcomes	Delay between the onset of 1 adenoma after complete resection of polyps and date of start of treatment (aspirin vs placebo) Number of patients who presented an adenoma during follow-up based on the gene reached (MLH1, MSH2, MSH6, PMS2, or without other identified anomalies) Load serrated polyps after 24 and 48 months of treatment

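### The primary end-point counts adenomas only at the planned M24 and M48 examinations, so a patient whose adenoma is removed at an extra colonoscopy, or who has cancer, can be analysed as a success

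*Protocol article*

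**What the plan says.** All references are to the protocol article.

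- **Primary end-point:** the outcome is the "number of patients with at least one adenoma detected during planned surveillance colonoscopies with chromo-endoscopy at 24 and 48 months". The next sentence reads: "Additional colonoscopies will be performed as required after initial colon clearance at inclusion with complete polyp removal". Nothing links what those examinations find to the outcome.
- **Follow-up visits and Table 2:** the visits provide for "additional colonoscopies scheduled as necessary". Table 2 lists chromo-colonoscopy as fixed at M24 and M48 and as conditional at M12 and M30.
- **Introduction:** colonoscopy is recommended every 2 years, and "every year when colonic neoplasia has been detected".
- **Secondary end-points:** cancers appear here and not in the primary outcome: "colon cancers diagnosed, and post-colonoscopy colon cancer (diagnosed between two planned surveillance colonoscopies"). The time-to-event outcome is "the delay between the inclusion and the first observed adenoma", with no restriction to planned examinations.
- **Statistical methods:** in the main analysis, patients lost to follow-up are failures in every group. No other route to failure is given.
- **Trial status, Table 3:** the registered primary outcome is "Number of patients with at least one adenoma seen on chromo-endoscopy 48 months after complete withdrawal of polyps". This adds no rule for findings in between.

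**The concern.** Polyps found at a colonoscopy are removed. An adenoma taken out at M12 is therefore not there to be seen at M24 or M48. If only the planned examinations count, a patient who developed an adenoma on study is recorded as adenoma-free unless another one appears.

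The loss is unlikely to be random. Under the recommendation quoted in the Introduction, patients with earlier neoplasia are the likeliest to be examined early, and the trial enrols patients for recurrence as well as first occurrence.

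Colorectal cancer, which adenoma prevention is meant to avert, is not a primary event in its own right. A patient with cancer who stays in follow-up without an adenoma at a planned examination is scored as a prevention success.

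Two things are at stake: events dropped from the main comparison, and a contrast that can shift if extra examinations, or what they find, differ between arms.

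**Working it through.** **1. Classification under the wording as it stands**

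| Course after randomisation | Primary outcome |
|---|---|
| Adenoma removed at M12 extra examination, M24 and M48 clear | success |
| Adenoma removed at M12, new adenoma at M24 or M48 | failure |
| Adenoma at M24, then an extra examination | failure already at M24 |
| M24 clear, adenoma removed at M30, M48 clear | success |
| Colorectal cancer, still followed, no adenoma at M24 or M48 | success |
| Colorectal cancer, then counted as lost | failure |

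Rows 1, 4 and 5 are the problem.

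**2. The plan's own sample size**

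Inputs from Sample size and Statistical methods: placebo 30%, relative reduction 28%, two-sided 5%, power 80%. Aspirin rate: 0.30 × 0.72 = 0.216. Mean rate: 0.258.

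n = [1.96·√(2·0.258·0.742) + 0.8416·√(0.30·0.70 + 0.216·0.784)]² / 0.084² = (1.2128 + 0.5184)² / 0.007056 ≈ 425 per group.

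The plan states 426, where power is 80.1%. The sample size reproduces and is not at issue.

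**3. Illustration of the loss**

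Assumptions, none from the document:
- 30% of patients have an M12 extra examination and a 12.5% yearly adenoma risk; the rest have 7%.
- The yearly risk is constant within each group.
- Every adenoma is seen at the next examination.
- The planned 30% is the rate over all examinations.

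Placebo:
- All events: 0.7·(1 − 0.93⁴) + 0.3·(1 − 0.875⁴) = 0.1764 + 0.1241 = 0.3005.
- Seen only at M12: 0.3·0.125·0.875³ = 0.0251.
- Counted: 0.3005 − 0.0251 = 0.2754. Share missed: 0.0251/0.3005 = 8.4%.

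Aspirin, with both yearly risks scaled by 0.689 so that the four-year rate is 0.72 × 0.3005 = 0.2164 (yearly risks 0.08614 and 0.04824):
- Seen only at M12: 0.3·0.08614·0.91386³ = 0.0197.
- Counted: 0.2164 − 0.0197 = 0.1966 (before rounding).

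Power at 426 per group = Φ{[d·√426 − 1.96·√(2·p̄·(1 − p̄))] / √(p₁q₁ + p₂q₂)}:
- All events, 0.3005 vs 0.2164: 80.2%.
- Planned only, 0.2754 vs 0.1966: Φ[(1.625 − 1.177)/0.598] = Φ(0.750) = 77.3%.

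The missed share depends on the assumed fraction s with an M12 examination. It equals s·0.125·0.875³ divided by the all-events rate. For s = 10%: 0.0084/0.2681 = 3.1%. For s = 40%: 0.0335/0.3167 = 10.6%.

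A simpler version removes the same share m from both arms of the planned 30% and 21.6%. With m = 5%, power is 77.4% (455 per group needed). With m = 10%, it is 74.4% (489 per group). The risk ratio stays at 0.72.

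**4. Unequal loss (assumed shares)**

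- 10% missed on placebo, 5% on aspirin: 0.270 vs 0.2052, risk ratio 0.76, power 60%.
- 5% missed on placebo, 10% on aspirin: 0.285 vs 0.1944, risk ratio 0.68, power 87%.

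**The case against.** The strongest reply is that the article does not expressly exclude findings from extra colonoscopies. The sentence about them stands in the end-point section, so the authors may have meant them to count, and the full protocol may say so. This is fair as to intent. However, the definition as printed names which examinations count, and a reader applying it would classify the patients above as successes. That is a stated rule, not a detail left out.

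The restriction also has a merit: fixed examinations give every patient the same number of looks. That stands, and it is why the planned-only version should be kept as a sensitivity analysis.

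Four stronger readings are tempting and are not supported:

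- **A false benefit for aspirin.** One might infer that bleeding on aspirin leads to more extra colonoscopies and so hides more adenomas in that arm. No section says bleeding or anaemia triggers a colonoscopy, active drug is masked within tablet size, and several bleeding-risk groups are excluded. Unequal loss can move the estimate either way.
- **Losses near a fifth of events.** That needs yearly examinations continuing to M36. Table 2 lists conditional examinations only at M12 and M30, eligibility asks for an indication for two-yearly surveillance, and a patient examined more often because of an M24 adenoma is already an event.
- **Total cancers set against the planned 8.4-point difference.** The first is a count over both arms and the second a contrast between arms. Only an imbalance in misclassified cancers would bias the result. Cancers are reported as secondary outcomes in any case.
- **A proven contradiction with the time-to-first-adenoma outcome.** That outcome names no examinations. That it includes extra ones is the natural reading, but still an inference.

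Power is lost only if the 30% describes adenomas at any examination. If it was meant for the end-point as defined, none is lost. The misclassification remains in both cases.

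**Conclusion.** The point holds as a defect of classification. The printed definition scores some patients with on-study neoplasia as successes, and the plan itself foresees the examinations that cause this. Nothing in the document gives the number of such patients. The 8% loss and the fall in power to about 77% are illustrative: they cover M12 examinations only, leave M30 aside, and rest on the assumptions listed. The assumption of one fixed yearly risk probably overstates the loss if adenomas recur in the same patients. Equal loss in both arms leaves the risk ratio about unchanged, and unequal loss biases it in a direction that cannot be told in advance. The case for changing the definition rests on the wrong coding of each affected patient, not on a demonstrated size or direction.

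**What to change.** - Define the primary event as at least one histologically confirmed adenoma or colorectal cancer at any colonoscopy (planned or extra) or surgery after randomisation, up to and including M48.
- Keep the planned-examinations-only, adenoma-only definition as a named sensitivity analysis.
- Report the number of extra colonoscopies by group.
- Align the primary outcome wording in Table 3 and the registry with the new definition.
- Make the change before treatment codes are broken, preferably before the 24-month intermediate analysis of secondary criteria.

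The cost is mainly wording and a registry update. Cancers and the number of follow-up chromo-colonoscopies are already to be reported; an extra examination done without chromo-endoscopy would have to be captured as well. There are two downsides. The outcome becomes a composite containing a few cancers. Patients with extra examinations also have more chances of detection, which the sensitivity analysis and the counts by group let the reader judge.

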### Secondary end-points

The secondary end-points are defined as the adenomatous polyp burden (calculated as the sum of adenomatous polyps diameters as measured during planned surveillance colonoscopies); the delay between the inclusion and the first observed adenoma; the number of patients who presented with an adenoma during the follow-up according to the affected gene (MLH1, MSH2, MSH6, PMS2, other or no abnormality identified); the number of patients with sessile serrated adenoma, colon cancers diagnosed, and post-colonoscopy colon cancer (diagnosed between two planned surveillance colonoscopies); and time of apparition.

The quality of bowel cleansing, the number of chromo-colonoscopies performed in follow-up sessions, the number of remaining tablets in blisters, and side effects are reported.

### Participant timeline

#### Screening visit

The selection period takes place up to 180 days before the inclusion visit. The investigator collects the patient’s personal history: characteristics of LS, genetic test results, and colonoscopy results. During this screening visit, the informed consent is given with the information notice.

#### Visit V0

The investigator first will obtain written consent from all patients. Inclusion and exclusion criteria will be checked. The first colonoscopy will be performed no longer than 180 days before the inclusion visit to assess pre-existing lesions. Colonoscopies will be performed according to INCa (Institut National du Cancer) recommendations. Colonoscopies may be performed outside the investigator’s hospital, including any public or private institutions. All identified polyps will be removed during colonoscopies prior to the inclusion visit. During each colonoscopy, patients are scored against quality criteria as defined by the Digestive Endoscopic French Society (SFED) guidelines [19]: adequately prepared bowel (Boston ≥ 7), cecal intubation rate ≥ 90% (complete visualization of the cecum and appendicular tripod, endoscope terminal located in the proximity of the appendiceal orifice confirmed by a photo or a video), appropriate polypectomy technique (biopsy forceps removal for polyps ≤ 3 mm in size and snare polypectomy for larger polyps), and withdrawal time ≥ 6 min. Adenomatous, sessile serrated adenoma and polyp burden will also be collected.

